## Abstract

**Background:**

The number of elderly people over the age of 65 commencing dialysis in NZ has increased by almost 400% in the past decade. Few data are available about health related outcomes and survival on dialysis in the elderly to help the individual, their family, clinicians and health planners with decision-making.

**Methods/design:**

This study will provide the first comprehensive longitudinal survey of health-related quality of life (HRQOL) and other patient centred outcomes for individuals aged ≥65 years on, or eligible for, dialysis therapy and will link these data to survival outcomes. Data collected by yearly structured interviews with participants will be linked to co-morbidity data, health service use, and laboratory information collected from health records, and analysed with respect to HRQOL and survival. The information obtained will inform the delivery of dialysis services in New Zealand and facilitate improved decision-making by individuals, their family and clinicians, about the appropriateness and impact of dialysis therapy on subsequent health and survival.

**Discussion:**

Results from this study will make possible more informed decision-making by future elderly patients and their families as they contemplate renal replacement therapy. Results will also allow health professionals to more accurately describe the impact of dialysis therapy on quality of life and outcomes for patients.

**Trial registration:**

ACTRN12611000024943.

## Background

There has been an increase of over 400% in the number of elderly and very elderly patients on dialysis in New Zealand over the past 2 decades [1]. This rapid increase has generated considerable debate resulting in wide variation in attitude towards referral and acceptance of elderly patients for dialysis [2-5]. One major reason for this is that there is uncertainty about the outcome from dialysis treatment in this population. Decision-making should, and clearly does, involve the patients and their carers’, along with health service providers. However, there is currently a dearth of evidence related to such decision-making among dialysis patients in general, and elderly dialysis patients in particular [6].

The assumption is often made that dialysis is appropriate for all individuals; however this may not be a valid assumption. Dialysis by the nature of the intervention has a large potential to negatively influence the quality of life of the individual and immediate family. While dialysis usually prolongs life in people with end stage kidney disease (ESKD), it has also been found that both patients and their partners are overwhelmed by the impact of dialysis on their lives [4]. Dialysis may substantially worsen quality of life especially in those with significant co-morbidity. However, if patients opt for conservative therapy (no dialysis) it is unknown how much life expectancy and quality of life is actually altered. There are currently few scientific data to inform and help clinicians, their patients and family to make a decision.

In addition to the impact of dialysis treatment on the individual, there is a significant health-economic implication for NZ, with the approximate cost of dialysis per individual at about $65,000 to $80,000 per year. In New Zealand, this equates to approximately $56 million per year for those on dialysis over the age of 65 years. This cost does not include the cost of hospitalisation and the impact of any other associated co-morbidity that is frequently present in the elderly and may be exacerbated by ESKD and/or its treatment. Although the crude cost for renal replacement therapy (RRT) can currently be estimated, there is no information about patient-experienced benefits to the individuals beyond survival.

The determinants of successful dialysis in the elderly will be multifactorial including the degree of autonomy or control related to managing dialysis (home care versus satellite or in-centre based care), and the many socio-economic factors related to the management of a chronic disease superimposed upon the aging process.

A recent study from a large London dialysis centre looked at outcomes between two groups of older patients, one group that opted for dialysis therapy and the other that chose maximal conservative care [6]. Those opting for conservative care were older (mean age 82 years versus 76 years). Although the dialysis group survived for a longer period (mean 2 years), the majority in the conservative group survived for over 13 months with substantially lower hospital days (16 days/per patient/year) and the majority in this group died at home [6]. The dialysis patients were dialysed in a hospital centre, that meant these patients averaged 173 days/per patient/year at the hospital. This study did not record any QoL assessment, data related to patient satisfaction, cost-effectiveness or the socio-economic impact of the hospital-based treatment [6].

In a thematic analysis of the literature Morton and colleagues demonstrated that awareness of factors associated with decision-making related to the management of CKD can provide health professionals with evidence on how best to deliver education programmes for patients and their family, as well as enhancing the patient and their family’s capacity to share in that decision making process [7]. They identified 4 themes – confronting mortality (life/death, burden on family, state of limbo), lack of choice (options not always discussed), knowledge of options, and weighing the alternatives [7]. These are the important issues that this study will focus upon.

It is vital for future health care delivery of renal replacement therapy in those aged ≥65 years in New Zealand that reliable data are obtained. It is also important to have accurate data upon which to base priority decisions regarding health funding and outcomes. In 2008, there were 154 new patients over 65 years commencing dialysis. This is a rate of 397 per million for elderly patients, compared to the overall rate of new patients for New Zealand at 109 per million [1].

### Aims

1) To determine the impact of age, sex, ethnicity, duration of dialysis, satisfaction with health services and co-morbidity on the health-related quality of life (HRQoL) in elderly patients (≥65 years) with chronic and end-stage kidney disease (CKD, ESKD).

2) Compare and contrast survival, health service utilisation, costs and HRQoL outcomes of older patients with EKSD according to the type of renal replacement therapy including modality (haemodialysis versus peritoneal dialysis) and location (home versus facility) or maximal conservative therapy (no dialysis).

3) To develop evidence-based guidelines for optimal management of older patients with severe CKD and ESKD.

### Hypotheses

From the cross-sectional data at baseline, we hypothesise that HRQoL differs between patients according to: sex, ethnicity, co-morbidities, type of dialysis treatment, health service satisfaction, costs, family support and duration of dialysis.

From longitudinal data in Years 2 and 3, we hypothesise that: HRQoL is positively associated with survival and that the HRQoL trajectory will differ between patients of different sex, ethnicity, co-morbidities, type of dialysis, availability of family and community support and duration of dialysis.

## Methods/Design

### Study design

The study uses an “accelerated longitudinal design”, comprised of cross-sectional and longitudinal components. The cross-sectional data are collected at the baseline interview and from clinical records in Year 1. The longitudinal data are collected from interviews 2 and 3 (12 and 24-months after the initial interview) and from clinical records in Years 2 and 3. This study design is optimal since it: 1) allows for the provision of timely results from an initial cross sectional analysis, and 2) by including the prevalent dialysis patients at baseline and the incident patients eligible for dialysis each year, it also allows for sufficiently powered longitudinal analyses, without the need for extended recruitment that would be necessary if the study used a dialysis inception cohort.

The nephrology teams responsible for their medical care have undertaken the identification of potential participants. All eligible (and consenting) participants will be contacted by telephone to arrange an interview. Data will be collected at each of the three interviews using structured questionnaires administered to participants by trained interviewers and from clinical records by the research nurses. The first Baseline Interview will be administered to all eligible participants already on dialysis for at least 90 days at the start of the study and to all new patients who are eligible for dialysis each year. Follow-up questionnaires are then administered to survivors 12 and 24-months later. The questionnaires have been piloted with 60 older patients with CKD and found to be acceptable and to cover questions and issues of greatest relevance to them [8]. Each interview will be designed to take 45-60 minutes and will be conducted either on the telephone or face to face depending on patient preference.

### Study participants

Our cohort will consist of dialysis and pre-dialysis patients recruited from three services across New Zealand, each serving different patient populations using contrasting models of care for dialysis delivery. These are: Middlemore Hospital (Counties Manukau District Health Board (DHB)), the largest dialysis service in New Zealand, providing both home and facility-based dialysis in mostly urban settings including a large proportion of New Zealand Māori and Pacific population; Dunedin Hospital (Southern DHB), a medium sized dialysis service providing entirely home-based dialysis in mixed urban and rural settings; and Hastings Hospital (Hawkes Bay DHB), a small sized dialysis service providing both home and facility-based dialysis in mostly rural settings. There is always a tension between the number of sites and speed of recruitment and the desire to carefully manage recruitment and the study process. By recruiting from three sites we ensure a range of participant characteristics in the study that are representative of New Zealand, while also ensuring that the study is efficient in terms of project management and data analysis. Using registry data from the Australian & New Zealand Dialysis and Transplant registry (ANZDATA), and a recruitment rate of 70%, it is estimated that we will enroll 160 to 172 prevelant participants and approximately 40 incident participants in the first year (Figure 1).

**Figure 1 F1:**
[figure not shown]
Presenting Recruitment and Follow-up (assuming an 70% response rate).

All patients will be followed prospectively including those who decide not to undertake dialysis, to explore changes in their HRQoL and survival status. The effects of age, sex, ethnicity, co-morbidities, modality, duration of dialysis treatment, family support and prior HRQoL on current quality of life and survival will be examined. Interview questionnaires include the SF-36 [9], the Kidney Disease Questionnaire [10] (KDQoL) EQ-5D [11,12]), WHODAS [13]. Inclusion of the KDQoL will make possible the comparison of the SF-36 health status of participants with other groups within New Zealand and will also provide kidney disease-specific information for comparing outcomes with international studies [14-17].

### Inclusion criteria

1) Prevalent dialysis patients under the three dialysis services aged ≥65 years who have been on dialysis for 90 days prior to survey date will be eligible to participate in the study.

2) Incident chronic kidney disease patients aged ≥65 years with an eGFR ≤15 ml/min/1.73 m^2^ presenting to the same services for consideration of dialysis will be eligible to participate in the study. A proportion of these patients will decide not to undertake dialysis. They will provide important data to compare and contrast with those who commence dialysis.

3) Patients aged ≥65 years who present with hitherto unrecognized renal failure requiring immediate dialysis will be eligible if their renal failure is deemed permanent by the treating nephrologist, and if dialysis is intended to be an indefinite treatment.

### Exclusion criteria

1) Inability to give informed consent

2) Inability to participate in a telephone or face-to-face interview

3) Inter current illness requiring hospitalisation (current and within 2 weeks of the survey period) and of sufficient severity to affect the patient’s ability to take part in the opinion of the treating physician (interviews for this last group will be rescheduled for 1 month later). Note that any selection bias introduced by this exclusion will be explored by comparison of survival of all patients from each unit.

### Data collected

#### Questionnaire

Most questions within the structured questionnaire are closed-response questions amenable to quantitative analysis. Most of these questions were trialled in a pilot study by us and found to be acceptable to patients [8]. The structured questionnaires also collect some information in ‘free-text/open-ended response’ format about participants’ decision-making about commencing dialysis, and dialysis type (haemodialysis or peritoneal) and their experience and perceptions of dialysis which will be analysed thematically. The interviews comprise

1. *Kidney disease* - The shorter version KDQol, [18-20] which includes the SF-36 [9] and Kidney Disease Questionnaire [10]. Inclusion of the KDQoL will make possible the comparison of the SF-36 health status of participants with other groups within New Zealand and also will provide kidney disease-specific information for comparing outcomes with international studies [14-17]. The KDQoL also includes a number of questions specifically enquiring about: managing kidney disease, CKD symptoms, effect of CKD on daily life and satisfaction with dialysis care.

2. *General Health Status* - EQ-5D. It is applicable to a wide range of health conditions and treatments; it provides a simple descriptive profile and rating of health status of use for within-study group comparison, economic analyses and for international comparison of health status outcomes [21]. New Zealand population norms are available for the EQ-5D (25) [22]. The alcohol use disorders identification test (AUDIT) was used to assess alcohol consumption [23] and some additional questions on illicit drug use using the AUDIT were added.

3. *Disability* - The WHODAS II, a short 12-question of measure of disability is one of few measures specifically designed to measure disability according to the World Health Organisation ICF model of disability [24]. Subjective wellbeing was measured using the Australian instrument, the Personal Well-Being Index [25].

4. *Social Supports:* 1) Residential status, including residential care and extended family support; 2) ability to perform independent dialysis treatment and/or any assistance required from family or friends; 3) what, if any, help is required by the patient around the home.

5. *Economic Burden and Personal Costs:* Three questions, modelled on the Ministry of Social Development sponsored study into the Living Standards of Older People [26] to discover financial burden for comparison with data from the general population. Information will also be collected about personal costs incurred as a result of dialysis [8].

6. *Mental health:* Depressive symptoms are common in chronic disease and have been shown to be related to survival in some studies [27] but not in others [28]. The relationship between depression and survival in the elderly dialysis population remains to be defined and there may be a positive relationship between age and emotional state [29]. We are measuring this with questions from the SF-36 scale and a question from the EQ-5D [9].

7. *Demographic data:* Data about ethnicity, descent from New Zealand Māori, household composition and home ownership will be collected as per the New Zealand Census [30].

#### Clinical records

1. *Co-morbidity:*Following participants consent, research staff will collect these data from participants’ clinical records. Co-morbidity may have significant influence on outcome with adverse effects on survival depending on specific conditions like diabetes, ischaemic heart disease and peripheral vascular disease [14]. Several indices of co-morbidity have been used for patients with chronic kidney disease and dialysis populations, for example: the Khan [31], Davies [32], and the Charlson [33] indices. However these were derived for general populations, not specifically CKD populations. We plan to utilise a newer improved co-morbidity index, validated against the USRDS end stage renal failure population, that is simpler, easier to use and has been shown to outperform the Charlson co-morbidity index [34]. It applies numerical weights to co-morbid conditions including atherosclerotic heart disease, congestive heart failure, cardiovascular disease, peripheral vascular disease, dysrhythmias, chronic airways disease, liver disease, cancer and diabetes. The sum of the weights present for the individual can be used as a continuous variable in analyses [34]. This will be linked to health service utilisation and adverse outcomes.

2. *Survival, other adverse outcomes, laboratory data and health service utilisation:* Data about survival, adverse outcomes, laboratory data and health service utilisation (including hospital admissions and length of stay) will also be collected from clinical records.

### Trial registration

Australian and New Zealand clinical trials registry: ACTRN12611000024943.

### Ethical approval

The study protocol was approved by the New Zealand Multi-Regional Ethics Committee, approval number MEC/10/084.

### Data analysis

All analyses will be performed using Stata 11.0 (or subsequent versions). Confidence intervals will be provided in all cases. All data will be described using appropriate summary statistics and frequency tables where necessary. Associations between the variables will be assessed in terms of statistical significance at a level of P <0.05.

### Cross sectional analysis from baseline data

Linear mixed models will be used to model quality of life measures (accounting for clustering within centres) based on subject demographics (including age, sex, ethnicity, socioeconomic status), co-morbidities, and modality and duration of dialysis. The prevalent dialysis participants will be grouped for analysis according to their vintage on dialysis, and combined for analysis with the incident patients in Year 1. Differences between categorical measures (e.g., ethnicity) will be assessed using adjusted means. Relationships between continuous measures (e.g., quality of life and dialysis duration) will be assessed using correlations. The study is powered at 80% to detect differences between means of 0.55 standard deviations for two groups sized 106 patients each (half of the sample), and differences of 0.8 standard deviations between two groups sized 53 patients each (quarter of the sample). These detectable differences are considered to be of clinical importance.

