### Longitudinal analysis

Mixed models will be used for the majority of the longitudinal analyses to estimate the trajectory of HRQoL over time. Correlation between repeated measures within centres and participant will be accounted for. Differences between groups at different time points will be assessed using adjusted means. Assuming a design effect of 2 for the quality of life instruments in the target population and a correlation of 0.65 between a participant’s repeated measurements, the study would be powered at 80% to detect changes as small as 0.45 standard deviations per six-month period within a group containing 38 patients.

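### With only three contrasting services, centre is better fitted as a fixed effect than as a clustering level in the HRQoL models, because ethnicity and dialysis location are tied to it

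*Protocol article*

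**What the plan says.** All references are to the protocol article.

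- *Cross sectional analysis from baseline data*: "Linear mixed models will be used to model quality of life measures (accounting for clustering within centres". The explanatory terms follow: "based on subject demographics (including age, sex, ethnicity, socioeconomic status), co-morbidities, and modality and duration of dialysis". Ethnicity is among them. Neither centre nor dialysis location (home or facility) is.
- *Longitudinal analysis*: "Correlation between repeated measures within centres and participant will be accounted for".
- *Study participants*: patients are "recruited from three services across New Zealand, each serving different patient populations using contrasting models of care for dialysis delivery". The largest service is described as "providing both home and facility-based dialysis in mostly urban settings including a large proportion of New Zealand Māori and Pacific population", the second as "a medium sized dialysis service providing entirely home-based dialysis in mixed urban and rural settings", and the third as "a small sized dialysis service providing both home and facility-based dialysis in mostly rural settings".
- *Aims*: Aim 1 includes the effect of ethnicity on HRQoL. Aim 2 compares outcomes by modality and by "location (home versus facility) or maximal conservative therapy (no dialysis".
- *Data analysis*: associations are judged at P < 0.05.

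**The concern.** The baseline analysis has one record per patient, and centre is the only grouping named. A linear mixed model then has no other random effect to carry, so a random centre intercept is the natural reading. The longitudinal text is less explicit: participant already supplies a random effect there, and centre could be handled in another way.

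A random centre effect has two requirements that this design meets poorly. First, its variance must be estimated, here from three values. When the estimate is zero, centre drops out of the model. Second, centre levels should be unrelated to the exposures. Here they are related by design: one service has no facility dialysis at all, and another is singled out for its Māori and Pacific share. When the variance estimate is positive but small, the model removes only part of any centre difference, and the rest goes to whatever exposure tracks centre.

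At stake are the ethnicity effect (Aim 1, a listed covariate) and any home versus facility effect (Aim 2). If the services differ in HRQoL for other reasons, such as rurality or service organisation, part of that difference would be reported as an ethnicity or location effect, with intervals that are too narrow.

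**Working it through.** **1. The plan's own figure.** Two-sided 5% test, 80% power, SD 1, each group divided by the design effect of 2 that *Longitudinal analysis* gives. Detectable difference = (1.960 + 0.842) × √(2 / effective n).

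- 106 per group, effective 53: 2.802 × √(2/53) = 0.544 SD (stated 0.55; power at 0.55 is 0.81).
- 53 per group, effective 26.5: 2.802 × √(2/26.5) = 0.770 SD (stated 0.8; power at 0.8 is 0.83).

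The stated power reproduces. Without the design effect it would be about 0.98 in both cases, so a design effect of 2 appears to have been used here too.

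**2. Implied intraclass correlation (ICC).** If that design effect is read as centre clustering (an assumption), with average centre size 212/3 = 70.7: ICC = (2 − 1) / (70.7 − 1) = 0.0144.

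**3. How much a random intercept removes.** With total variance 1, the fraction of a centre mean removed is n·ICC / [1 + (n − 1)·ICC] = (70.7 × 0.0144) / 2 ≈ 0.51. Even with the variance known exactly, about half of a centre difference is left in an average-sized centre.

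**4. Simulation with no true exposure effect.** N = 212 (2 × 106), three centres; random intercept with a Wald z test against two centre indicators with a t test. From the document: three centres and 100% home in one. Assumed: centre sizes, the other home shares, the ethnic shares and the ICC. Shares are in the order largest / all-home / small service. Each row is 6,000 runs (Monte Carlo SE about 0.3 points at 5%); cells give the percentage with P < 0.05.

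| Exposure and shares (%) | Sizes | ICC | Random, ML | Random, REML | Fixed | REML variance = 0 |
|---|---|---|---|---|---|---|
| Home 50/100/50 | 120/55/37 | 0 | 5.6 | 5.4 | 5.4 | 64% |
| Home 50/100/50 | 120/55/37 | 0.0144 | 6.3 | 5.9 | 5.2 | 44% |
| Home 30/100/50 | 120/55/37 | 0.0144 | 8.1 | 7.0 | 5.6 | 44% |
| Home 30/100/50 | 71/71/70 | 0.0144 | 7.7 | 6.7 | 4.8 | 42% |
| Home 30/100/50 | 120/55/37 | 0.05 | 9.9 | 7.9 | 5.2 | 26% |
| Māori/Pacific 70/10/40 | 120/55/37 | 0.0144 | 7.1 | 6.3 | 5.0 | 43% |
| Māori/Pacific 70/10/40 | 71/71/70 | 0.0144 | 6.7 | 6.2 | 5.3 | 41% |

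With the exposure balanced across centres, the random-centre test stays at 4.3–6.2% (1,500 runs per setting).

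**5. All-home service shifted by a fixed amount.** Sizes 120/55/37, 1,500 runs (Monte Carlo SE about 0.6 points). Cells give % rejected, with bias in SD in brackets.

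| Exposure | Shift (SD) | Random, ML | Random, REML | Fixed |
|---|---|---|---|---|
| Home 30/100/50 | 0.2 | 10.3 (0.077) | 8.9 (0.056) | 5.3 (0.001) |
| | 0.3 | 13.3 (0.099) | 9.9 (0.067) | 4.5 (−0.003) |
| | 0.5 | 18.1 (0.114) | 10.9 (0.072) | 4.9 (0.004) |
| Māori/Pacific 70/10/40 | 0.2 | 9.2 (−0.060) | 7.8 (−0.044) | 5.2 (−0.004) |
| | 0.3 | 11.7 (−0.074) | 9.5 (−0.051) | 6.1 (−0.001) |
| | 0.5 | 10.3 (−0.069) | 7.3 (−0.044) | 4.5 (0.000) |

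A second simulation (sizes 120/60/32, home 35/100/50%, REML, 2,000 runs) agrees. Shifts of 0.2/0.3/0.4 SD give 8.4/9.6/11.6% rejection, bias 0.055/0.065/0.069 SD, and a centre variance of exactly zero in 47/30/15% of runs. Fixed centre gives 4.8–4.9%.

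**6. Price of fixed centre terms.** SD of the estimate at ICC 0.0144, fixed against random REML: 0.159/0.152 = 1.05 and 0.171/0.158 = 1.08. In the second simulation, 0.170 against 0.147–0.156, a ratio of 1.09–1.16.

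Only the cross-sectional model was simulated, and every participant was given a dialysis location, although some of the incident group will not be on dialysis.

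**The case against.** - **The random effect is inferred.** The article never says random intercept, and a condensed article may leave the parameterisation to a fuller plan. This carries weight for the longitudinal model, less for the baseline model, where the stated method and single grouping leave little else. If fixed terms are intended, one sentence settles it.
- **The design effect already allows for clustering.** It enlarges the variance used to plan power. It neither removes confounding by centre nor protects the error rate of the fitted model.
- **Location is not in the listed model.** This stands. The baseline covariates include modality and duration, not home versus facility. The location point applies to whatever model serves Aim 2; the ethnicity point applies to the listed model directly.
- **The bias is small.** This also stands: 0.05–0.08 SD is about 9–15% of the 0.55 SD that the plan calls clinically important. Nothing shows that a conclusion would change.
- **The remedy alters the question.** Also true. With centre fixed, the all-home service no longer informs home versus facility, and selection of individual patients to home dialysis within the other two services can still confound. The absence of bias under fixed centre terms holds only because the simulation contains no such selection.

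**Conclusion.** The point holds in conditional form. Treating three purposively contrasted services as a clustering level gives unreliable adjustment for centre, and ethnicity and location are tied to centre. If the services truly differ, the nominal 5% test rejects in about 6–8% at the ICC implied by a design effect of 2. If one service is shifted by 0.2–0.4 SD or more, it rejects in about 8–12% for location, with bias of about 0.05–0.08 SD, and in about 7–10% for ethnicity under REML. ML, which the article neither chooses nor excludes, is worse. These sizes rest on assumed centre sizes, home and ethnic shares and centre differences.

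A reader might infer that the error rate exceeds 5% outright, or that the location and ethnicity effects are merely one hospital against another. The documents do not support either: with no centre differences, or with exposure balanced across centres, the rate stays near 5%, and the article gives no figures on how the services differ in HRQoL. Nor is the power calculation at fault, since it reproduces.

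**What to change.** In both HRQoL analysis sections, state that centre enters as a fixed effect (two indicator terms for three services). Keep a random effect for participant in the longitudinal model only; the baseline model then needs no random effect. Add that home versus facility is a within-service contrast drawn from the two services offering both, that it remains open to patient-level selection, and that any comparison involving the all-home service will be reported descriptively as a difference between services.

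The change takes two or three sentences and no new data. It costs a standard error about 5–15% larger for exposures tied to centre, and a location contrast that rests on two services instead of three.

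### The only stated ethnicity and sex contrasts in baseline HRQoL are adjusted for factors that may carry part of the difference; report a less-adjusted contrast beside them

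*Protocol article*

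**What the plan says.** Aim 1 is "To determine the impact of age, sex, ethnicity, duration of dialysis, satisfaction with health services and co-morbidity on the health-related quality of life" in older patients with chronic and end-stage kidney disease. The Hypotheses section says of the baseline data: "we hypothesise that HRQoL differs between patients according to: sex, ethnicity, co-morbidities, type of dialysis treatment", followed by further factors.

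The section on the cross-sectional analysis of baseline data states the method: "Linear mixed models will be used to model quality of life measures (accounting for clustering within centres"), with the models "based on subject demographics (including age, sex, ethnicity, socioeconomic status), co-morbidities, and modality and duration of dialysis". It then says how group contrasts are obtained: "Differences between categorical measures (e.g., ethnicity) will be assessed using adjusted means". Continuous relationships, with HRQoL and dialysis duration as the example, are to be assessed by correlations.

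The general Data analysis section adds "All data will be described using appropriate summary statistics and frequency tables where necessary" and sets "statistical significance at a level of P <0.05". No section says whether Aim 1 means the overall difference between groups or the difference left after other factors are accounted for. None gives a separate covariate set for any factor.

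**The concern.** Ethnicity and sex precede the other listed covariates. A person's socioeconomic position, burden of illness, dialysis modality and time on dialysis cannot cause their ethnicity or sex, but can be shaped by them. The article itself expects some of these to matter: the Background says dialysis may worsen quality of life, especially with significant co-morbidity, and the Clinical records section expects co-morbidity to influence outcome.

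An ethnicity mean adjusted for all of them compares groups as if their wealth, illness and treatment were equal. That is a useful question, but a different one from whether HRQoL differs by ethnicity. If the adjusted contrast is the only one reported, a non-significant result may be read as no disparity when the disparity runs through co-morbidity or modality. This matters here because one of the three services was described as having a large Māori and Pacific population, and the results are meant to inform service delivery and guidelines.

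**Working it through.** **1. Question against estimator, for ethnicity and sex**

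| | What the article states | What it yields |
|---|---|---|
| Question (Aims, Hypotheses) | Impact of the factor; HRQoL differs by it | Most directly, the difference between groups |
| Covariates (cross-sectional analysis) | Age, sex, ethnicity, socioeconomic status, co-morbidities, modality, duration | Includes possible consequences of ethnicity and sex |
| Contrast (cross-sectional analysis) | Adjusted means | The difference not explained by the other covariates |

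The promised descriptive summaries are not specified by ethnic group or sex, and would not be adjusted for age.

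**2. The plan's own detectable difference**

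Inputs: 0.55 SD, 106 per group and 80% power (cross-sectional section); 5% level (Data analysis), taken as two-sided; design effect 2, stated only in the Longitudinal analysis section but needed to recover the figure.

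- Effective n per group = 106 / 2 = 53.
- Standard error = √(2/53) = 0.194 SD.
- Detectable difference = (1.960 + 0.842) × 0.194 = 0.544 SD.
- Power at 0.55 SD = Φ(0.55/0.194 − 1.960) = 80.8% (80.1% with the t distribution).

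The stated figure reproduces. Without the design effect, power would be 98%.

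**3. How far adjustment could move the contrast (assumption only)**

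In a linear model, the overall difference equals the adjusted difference plus the sum over pathways of (group gap on the covariate × slope of HRQoL on it). The documents give no gap or slope. Assume two pathways, socioeconomic status and co-morbidity, both acting in the direction of the overall difference, with gaps of 0.3 to 0.5 SD and slopes of 0.2 to 0.3 SD of HRQoL per SD.

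- Low end: 2 × 0.3 × 0.2 = 0.12 SD, which is 0.12/0.55 = 22% of 0.55 SD.
- High end: 2 × 0.5 × 0.3 = 0.30 SD, which is 0.30/0.55 = 55% of 0.55 SD.

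**4. Consequence, if the overall difference were 0.55 SD**

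With 106 per group, design effect 2 and SD held at 1:

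| Removed by adjustment | Left | Power of the adjusted contrast |
|---|---|---|
| 0 | 0.55 SD | 81% |
| 0.12 SD | 0.43 SD | Φ(0.43/0.194 − 1.960) ≈ 60% |
| 0.30 SD | 0.25 SD | Φ(0.25/0.194 − 1.960) ≈ 25% |

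These powers are rough: adjustment also lowers the residual SD, and ethnic groups need not split the sample in half. If both pathways ran the other way, the same arithmetic would enlarge the contrast, to 0.55 + 0.12 = 0.67 SD or 0.55 + 0.30 = 0.85 SD. If they ran in opposite directions with equal size, it would not move.

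**The case against.** Several points on the other side stand and limit the finding.

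- **One model for everything.** A reader might infer that every factor's effect comes from a single fit containing all the others. The article does not say so. It speaks of models in the plural and does not exclude unadjusted or stepwise fits. Its list is evidently not a full specification, since satisfaction with health services, named in Aim 1, is missing from it.
- **Age, duration and co-morbidity.** A reader might extend the point to every Aim 1 factor. The text does not support that. It assigns continuous relationships to correlations, with duration as its example; age is naturally continuous, and the co-morbidity score may be used as such. The point is firm only for ethnicity and sex.
- **Meaning of impact.** The word need not mean an overall effect; an independent association is a fair reading.
- **Direction.** Attenuation requires the pathways to act in the same direction as the overall difference. Adjustment can also enlarge it.
- **Level of detail.** Covariate sets for each factor usually belong in an analysis plan, which is not shown, and a journal article condenses.

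The last objection does not dispose of the point. The article goes beyond silence: it names the covariates and says that ethnicity is read from adjusted means. As written, that is the only stated ethnicity contrast, and it sits beside a hypothesis worded as a difference between patients.

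**Conclusion.** The point holds in a limited form. For ethnicity and sex, the stated contrast is conditional on variables that may be consequences of them, so it gives the unexplained part of the difference. Aim 1 and the baseline hypothesis can be answered fully only if the overall difference is reported as well.

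This does not show that the planned model is wrong, that any real difference will be missed, or that the stated power figures are in error; the 0.55 SD figure reproduces with a design effect of 2. The size is unknown. The 0.12 to 0.30 SD rests on assumed gaps, assumed slopes and two same-direction pathways, and serves only to show that the change could be material against 0.55 SD.

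**What to change.** For ethnicity and sex, state that two sets of adjusted means will be reported for each HRQoL measure:

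1. From a model with age, sex, ethnicity and centre, labelled as the overall difference.
2. From the model with all listed covariates, labelled as the difference not explained by socioeconomic status, co-morbidity and treatment.

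Add a note that centre may itself carry part of the ethnic difference. The three services differ in both population and delivery: one has a large Māori and Pacific population and offers home and facility dialysis, while another is entirely home-based. The first contrast is therefore an overall difference within centres, not a complete total effect.

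The cost is one or two extra model fits and one table column, on data already collected. Recruitment, questionnaires and the sample-size statement do not change.
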